## Methods: Participants, interventions and outcomes

### Ethics and dissemination

The trial was granted Andalusian Research Ethics Committee (S2 File; 202167133116; 202072112495; 2021128101651) and the Regional Committees on Health Research Ethics for Southern Denmark (20212000–80). Any changes to the protocol are subject to a formal amendment and may not be implemented prior to the approval by the Research Ethics Committee of each country.

### Study setting

Participants will be recruited at twenty-nine urban public primary health antenatal care centers within Andalusia (Spain) and at Odense University Hospital in the Region of Southern Denmark. Participants will be randomised to the intervention group or to the control group (Fig 2).

### Eligibility criteria

All women who fulfil the inclusion criteria will be screened and invited to receive an e-health package. Of those who accept the e-health intervention, 20 women will be randomised, 10 women in each country. In Spain and Denmark, respectively, 5 will be allocated in the intervention group and 5 will be asked to consent to be in the control group.

Inclusion criteria: pregnant women at <12 weeks gestation, who screen positive in IPV at the first antenatal visit and accept the e-health package.

Exclusion criteria: (1) women who cannot be informed about the study without their partners or other family members knowing; (2) mentally or physically incapacity to participate in the study; (3) women below 16 years in Spain or below 18 years in Denmark; (4) inability to understand Danish/Spanish, (5) lack of internet and electronic device and (6) women with extreme severity of IPV. Women selected to participate in the trial in this situation will receive an evaluation of danger before randomisation. If the severity of IPV is confirmed to be at high level of danger, these pregnant women will be routinely treated and supported according to the standard protocol in each country. Following this path, any potential risk for the women will be taken into account from the beginning of the process and women will be protected. Women who have same-sex partners will be screened, but their data will not be used for the purpose of this study.

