## Abstract

Intimate partner violence (IPV) during pregnancy, a condition as common as obstetrics conditions like gestational diabetes, is associated with maternal and neonatal complications. Systematic detection of IPV is not well established in antenatal screening probably because the effectiveness of protective interventions has not been evaluated. E-health interventions may be beneficial among mothers exposed to IPV. Prior to performing a full-scale effectiveness trial for such an intervention, a pilot study is required to assess the feasibility of randomising a sufficiently large number of women exposed to IPV during pregnancy. The eIPV trial is a randomised pilot study nested within a cohort of consenting mothers who screen positive for IPV in the first antenatal visit at <12 weeks’ gestation and accept an e-health package (psychological counselling by videoconference) in Spain and Denmark. Twenty eligible mothers from the above cohort will be randomised to either intervention or control. The intervention group will receive the e-health package as part of the cohort. The control group will be invited to accept a delay in the intervention (e-health package eight weeks later). After consenting to delay, the control group will provide comparative data without losing the opportunity of obtaining the intervention. We will determine estimates of rates of informed consent to randomization, and the rates of adherence and dropout following randomization. Qualitative interviews will be conducted to examine the women’s perception about the benefit of the intervention, reasons for acceptability and non-adherence, and obstacles to recruitment, randomisation and consent. The results will inform the trial feasibility and variance of key clinical outcome measures for estimation of sample size of the full-scale effectiveness trial.

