**Fig 2 pone.0282997.g002:**
[figure not shown]
Flowchart of eIPV trial.

In the second stage, participants who have been assigned to the control, will be reapproached and given information about their participation in the control group. At this stage, they will be invited to accept a delay in the intervention (e-health package eight weeks later) and be asked to give the second informed consent for a delayed intervention. Those who decline will remain in the cohort study. Those in the cohort only group will not be informed about the randomization, as their subsequent follow up in the study will remain part of the cohort study to which they would already have consented in the first stage. We will substitute the women who not consent being part of the control until we reach the sample required (5 women in each country). This information will be also analysed for a future full-scale RCT.

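### Twenty is the number of women retained, not the number randomised, because women who decline the control group are replaced after allocation

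*Protocol article*

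**What the plan says.** The protocol article gives the size twice as a number randomised.

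- Abstract: "Twenty eligible mothers from the above cohort will be randomised to either intervention or control".
- Eligibility criteria: "Of those who accept the e-health intervention, 20 women will be randomised, 10 women in each country". Within each country, "5 will be allocated in the intervention group and 5 will be asked to consent to be in the control group".

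The second stage under Trial design (the text after the Fig 2 caption) sets the order of events and the replacement rule.

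- Assignment comes before the second consent: "participants who have been assigned to the control, will be reapproached and given information about their participation in the control group".
- Decliners leave the comparison: "Those who decline will remain in the cohort study".
- They are replaced: "We will substitute the women who not consent being part of the control until we reach the sample required (5 women in each country").

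Randomisation procedures confirms that women are allocated once they accept the package, at a ratio of 1:1. The outcome list treats recruitment as complete when each country has five intervention and five control women. The primary outcome is the rate of consent to the control group, and Statistical analysis reports it with a 95% confidence interval.

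**The concern.** Asking five women per country and asking until five accept are the same only if nobody declines. The protocol expects refusals. The Discussion gives women's likely reluctance to be in a control group as the reason for the modified Zelen design, and estimating acceptance is the pilot's main aim.

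Three things depend on which description governs:

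- **The number randomised.** Women in the intervention group are randomised without being told, so this figure should be stated correctly.
- **The denominator of the primary rate**, which is the number of women asked. It is 10 on the Eligibility wording and about 10/p under substitution.
- **The recruitment duration**, a listed secondary outcome, which lengthens as more women have to be asked.

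**Working it through.** **Inputs**

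| Input | Value | Where in the protocol article |
|---|---|---|
| Stated number randomised | 20 (10 per country) | Abstract; Eligibility criteria |
| Group sizes per country | 5 intervention, 5 control | Eligibility criteria; outcome list |
| Order | assignment, then second consent | Trial design, second stage |
| Replacement | until 5 consenting controls per country | Trial design, second stage |
| Ratio | 1:1 | Randomisation procedures |
| Consent thresholds | Go >25%, Stop <10% | Table 1 |

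The protocol gives no expected second-consent rate, so p is an assumption and is shown over a range. The same p is assumed in both countries.

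**Step 1. Reproduce the stated figure.** 2 countries × (5 + 5) = 20. This is the sum of the completed groups. Sample size calculation contains no power-based figure to check.

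**Step 2. When is 20 also the number randomised?** Only when the first 10 women assigned to control all accept, with probability p^10:

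- p = 0.9: 0.349
- p = 0.8: 0.107
- p = 0.5: 0.00098
- p = 0.25: about 1 in a million

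**Step 3. Expected number randomised.** Asking until 10 accept is negative binomial sampling, so the expected number asked is 10/p. There are two readings for the substitutes:

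- A: substitutes go to control only and intervention stays at 10. Total = 10 + 10/p.
- B: the 1:1 ratio is kept for every substitute. Total = 2 × 10/p = 20/p.

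| p | Asked, 10/p | A: 10 + 10/p | A: approx. 95% range | B: 20/p |
|---|---|---|---|---|
| 0.80 | 12.5 | 22.5 | 20 to 27 | 25 |
| 0.50 | 20 | 30 | 23 to 40 | 40 |
| 0.25 | 40 | 50 | 32 to 75 | 80 |
| 0.10 | 100 | 110 | 61 to 177 | 200 |

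Reading A departs from the 1:1 ratio. Reading B departs from five intervention women per country: at p = 0.25 it allocates 40 to intervention where 10 are planned. The article does not say which applies.

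**Step 4. Effect on the primary rate.** This step takes Table 1's consent criterion as the second consent.

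- With 10 women asked in total, a rate below 10% requires 0 of 10. When true consent is 10%, that has probability 0.9^10 = 0.349.
- With substitution run to completion, the number of acceptors is always 10. A rate below 10% then requires 10/x < 0.10, that is, more than 100 women asked.

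The two descriptions are different sampling schemes and reach Stop in different ways.

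**The case against.** The strongest reply is that the mechanism is disclosed. The article states the substitution openly and says the information on decliners will be analysed. Its outcome list calls five plus five per country the pilot sample. Recruitment: Consent procedures describes the second consent as permission to be allocated to the control group. On that view the article uses randomised loosely for women who complete allocation, and 20 is simply the target. There is no power calculation to upset, and decliners stay in the cohort. This limits the consequence, but it does not reconcile the text: five asked per country and asking until five accept still conflict once one woman declines.

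A reader might infer more than the article supports, in four ways.

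- **That 50 to 110 women would be randomised.** This needs reading A, and it needs Table 1's eligible women agreeing to participate to mean the second consent. Eligibility criteria supports that, because eligibility already requires accepting the package, and so does the primary outcome. But Screening procedures applies the word eligible to women not yet screened, and Table 1 is silent.
- **That the pilot has no end point.** No numeric ceiling is stated, but Trial status gives September 2022 for completing recruitment, which is a practical bound, and the advisory board monitors recruitment.
- **That 20 is the denominator of the primary rate.** It is not; the number asked is.
- **That a ceiling of 50 invitations per country would settle the matter**, because a short control group would imply Stop. Countries close separately: 5 of 5 in one and 4 of 50 in the other gives 9/55 = 16%, which is in Table 1's reassess zone.

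**Conclusion.** The point holds as an inconsistency between the stated size and the design. The Abstract and Eligibility criteria report the number retained as the number randomised, and the number who must accept as the number asked. Both statements are true only if no woman assigned to control declines.

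The size of the gap depends on the unknown p and on how substitutes are allocated. It is small at high acceptance (22.5 or 25 against 20 at p = 0.8) and large at low acceptance (50 or 80 at p = 0.25; 110 or 200 at p = 0.10). These are expected values. Tying the last two rows to the Go and Stop thresholds is conditional on Table 1 referring to the second consent.

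The correction should be made because the number asked is the denominator of the primary outcome. The inconsistency does not invalidate the pilot.

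**What to change.** 1. In the Abstract and Eligibility criteria, restate the size as 20 women retained (5 + 5 per country), with the expected number randomised given as 10 + 10/p and tabulated over a range of p. If 1:1 is kept for substitutes, use 20/p.
2. In Eligibility criteria, replace "5 will be asked to consent to be in the control group" with wording that five consenting women per country will form the control group, to match the substitution rule.
3. State whether substitutes are allocated to control only or 1:1, and align Randomisation procedures with that choice.
4. Define the denominator of the primary rate as all women assigned to control and asked, decliners included.
5. State in Table 1 which consent its first criterion refers to.
6. A ceiling is optional. If one is wanted, apply it to the pooled rate: close when 100 women have been asked across both countries with fewer than 10 acceptors. The rate is then at most 9/100 = 9%, below the Stop threshold if Table 1 refers to the second consent. Do not set a ceiling per country.

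The cost is a less tidy stated size and a formal amendment, which Ethics and dissemination requires to be approved in each country. No extra data collection is needed.

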### Recruitment: Consent procedures

In advance, a written, informed consent (in Spain the informed consent will be oral and recorded) for administering the screening of IPV, will be sought from the pregnant women at the first antenatal visit with a midwife. Those who screen positive, will also be asked for consent to receive the e-health package intervention and to complete baseline and outcome measurement questionnaires (one month after the intervention). For the pilot trial, women who consent to receive the e-health package will be randomized (following a modified Zelen’s design) into the intervention group (without their knowledge) or into the control group. Women in the control group will additionally be asked for a second informed consent, to be allocated in this group and to receive the e-health package 8 weeks later. This approach is suggested by the input of IPV survivors. A few women from the intervention and control groups of the pilot trial will be asked for consent to be contacted for a qualitative interview. Women will be informed that they have the right to refuse participation as well as to withdraw their consent at any time, without giving a reason, and that this will not affect their subsequent care. If they withdraw consent, data collected up to the point of withdrawal will be retained in the study. Participant information sheets and consent forms used for this pilot study are available on request from investigators. The informed consent provides study aims, contact details and sources for further information. Given the importance of taking into consideration the views and opinion of the participants [25], all recruitment materials have been developed with significant input from a patient and public involvement (PPI) group consisting at two participant representatives from Spain and Denmark (see the Discussion section).

### Screening procedures

Eligible women are invited by trained midwives at the first antenatal care visit to fill in an app developed for tablets for the screening of IPV during pregnancy (in Spain). In Denmark, screening for IPV is part of routine antenatal care in the Region of Southern Denmark where pregnant women are asked to fill in an electronical questionnaire on health conditions and pregnancy related life-style measures in the first trimester (PRO-data), including a screening for IPV exposure.

Women who screen positive in IPV will be invited to receive an e-health intervention (see the positivity criteria in the data collection section below).

### Randomisation procedures

The research team will consult the data server on a daily basis to identify women who screen positive in IPV and accept to receive the e-health package to randomly allocate them (using a computer-generated random numbers) in the intervention or control group through randomisation at a ratio of 1:1. IPV counsellors will be informed of the assignments to each group. Women in the intervention group will be blinded but not women in the control group.

### Study interventions and assessments

Intervention group: Women positive for IPV who accept the e-Health intervention and who have been randomly allocated in the intervention group will receive the e-health package as the rest of the cohort, as well as the baseline and outcome measurements. The e-health package will include six video counselling sessions by trained providers—a psychologist in Spain; midwives in Denmark. Women in both countries will be provided access to a mobile app for designing security plans. This will be an adapted version of the mobile app “My Plan”. To organize and host the video counselling sessions the platform “Linkello Medical” will be used in Spain and the app “My Hospital” will be used in Denmark. Both allow health providers to interact with the women in the place they prefer as long as they have Internet connection. In “Linkello Medical”, the psychologist will send an Internet link to the women by her preferred means (via mobile message or by email) and she would just have to click on the link to connect. Women will not need to register nor provide any personal data. The link will be volatile, i.e., it will be not reusable after completion of the communication. In “My Hospital”, is a software developed specifically for confidential hospital-patient communication in the Region of Southern Denmark and is already used in antenatal care as a regular communication tool. When the pregnant woman attend her first antenatal care visit, she will be introduced to My Hospital and instructed in how to access the system via the Internet or a mobile app. The midwives book the women for a video call through the system. Fifteen minutes before the video call is starting, the woman receives a notification to accept the call. Once the woman has accepted the call, the midwife can start the video consultation. This easy and confidential way of interaction will facilitate women’s participation. The mobile app for safety planning will be camouflaged to look like a common pregnancy app. The content and setup of the safety planning app was adapted from the interactive safety decision aid developed by Glass, et al. [26] which is freely available. A safety plan is a personal and practical plan, designed by a woman exposed to violence to minimize their risk of danger and exposure to violence. By digitalizing the safety plan into an app, the women will always have it available to remind them of their own strategies and resources. The safety planning element will be hidden inside the pregnancy app for security reasons; the women must log on for this element to be opened. Once a woman has logged on, the front page consists of two buttons, “Help” and “Emergency”. Both buttons consist of default contact information for relevant resources which can help a woman in case she needs help or is in an emergency situation. The woman can edit the information to fit her own needs. The app also includes the following features: “Warning signs”, where the woman can add signs that may trigger situations where violence could occur; “Strategies”‘, where the woman can note down her coping strategies; and, “Diary”, where a woman can write down anything of importance. It will also contain the feature “Knowledge about domestic violence” which will provide information and links to local and national resource’s relevant for women exposed to violence. Under another feature called “Quick Messages” a woman can enable a predetermined message to her emergency contacts. In case the woman needs to exit the app quickly, she will be able to press the “Quick-exit” button, where she will immediately return to the camouflaged part of the app. This app has been made freely downloadable to researchers and users for both android and iOS devices.

We will monitor if participants adhere to all the sessions offered for counselling and in case of non-adherence or failure to engage in counselling, the counsellor will follow specific protocol to encourage reengagement. In Spain, the psychologist will contact the woman two to three times through the preferred mean (email or phone). In Denmark, a project midwife will try to contact the woman on the preferred mean (email or phone) at 3 occasions within 6 weeks. The content of the six individually tailored sessions will be based on the Dutton’s Empowerment Model [27] and the Psychosocial Readiness Model [28]. Specifically, the contents will include (session 1) the evaluation of abusive behaviour (which will also served to protect the pregnant women is the level of violence detected is high); (session 2) safety planning, network and resources; (session 3) psycho-education (healthy relationships, cycle of violence…); (session 4) self-esteem and self-care and (sessions 5 & 6) empowerment, choice making and problem solving. The video consultations will be planned for every 2 weeks at a time where the women feel comfortable. However, schedule flexibility will always prevail to promote women participation. Criteria for discontinuing or modifying allocated interventions will be applied to women with an elevated risk for IPV who will be routinely treated according to the standard protocol in each country. In other words, if during the interventions the health providers detect an increased on the level of violence, they will apply the established national protocols to protect the pregnant women.

Control group: IPV positive women who accept the e-Health intervention package will be asked for a second consent to receive a delayed intervention (8 weeks later) and to complete the baseline and outcome measurements. Women can request to leave the control group at any time and receive the intervention immediately (in which case the data will be part of the cohort study).

Assessments and data collection: data on socio-demographic characteristics and partner violence will be collected during the screening process. The validated screening questionnaires to detect IPV will be the short form of the Women Abuse Screening tool (WAST-Short) [29], a 2-items tool that measures conflict and tension and the Abuse Assessment Screen (AAS) [30], a 5-item screening questionnaire including emotional, physical, and sexual violence as well as fear of partner within the past year or ever. Data from previous studies support the reliability and validity of the WAST [31] and the AAS [30]. In Spain, a woman is initially screened positive for exposure to IPV in the AAS if she answers “yes” to one or more of the five questions if the perpetrator is the partner or ex-partner. In Denmark, a woman screen positive if she answers “yes” to having been afraid of their partner or ex-partner or to having been exposed to emotional, physical or sexual violence within the past 12 months by a partner or ex-partner in the AAS. In Spain, a woman screens positive in WAST-Short if she meets one of the two original criteria: (1) having some or a lot of tension and/or some or a lot of difficulties to solve problems with her partner (all positive responses receive 1, the cut-off = 2) or (2) if she indicates having a lot of tension and/or a lot of difficulties (extreme responses receive 1, cut-off = 1). In Denmark, woman screens positive in WAST-Short if she meets the second criteria. If the women initially are screened positive, the screening questionnaires will automatically be followed by the Index of Spouse Abuse (ISA) questionnaire [29]. The ISA questionnaire is a detailed 30-item questionnaire about IPV (emotional, physical and sexual) in order to confirm the IPV and evaluate the severity of the violence. Two different scores are computed: ISA-P (physical abuse) and ISA-NP (non-physical abuse). The scores range from 0 to 100. In Denmark, the cut-off scores of 10 for ISA-P, and 25 for ISA-NP developed by Hudson and McIntosh will be used [32]. In Spain, based on the Spanish validation of the ISA tool [33] that gives different weights to the original items, cut-off scores of 6 for ISA-P, and 14 for ISA-NP will be applied. The reliability (α) of the ISA range from .82 [33] to .96 [32].

Quantitative questionnaire data will be collected before and after the e-health intervention. Exposure to IPV will be assessed by use of the ISA tool, and post-natal depression will be assessed by use of The Edinburgh Postnatal Depression Scale (EPDS, α = .81) which is a 10-item validated questionnaire designed to detect postnatal depression [34]. Further, participants will be asked to assess their ability to carry out safety behaviour actions by use of a revised version of the 22-item safety action checklist (α = .75) [35] and to complete a Measure of Victim Empowerment Related to Safety (MOVERS; α = .74-.88) [36] All the data will be entered into a bespoke secure online study database using a unique study ID for each participant. The health providers will check the items of the ISA related to physical IPV and the psychological IPV items measuring fear of the partner to determine if the women invited to the pilot are at extreme level of IPV risk. In those women who respond positive to the above items, before randomisation the providers will evaluate the level of danger with the Severe Intimate Partner Violence Risk Prediction Scale-Revised (EPV-R, α = .72) [37]. If the level of danger is confirmed to be high, women will not be included in the study and will be routinely treated and supported according to the standard protocol in each country.

Qualitative data will be collected through individual in-depth interviews with a few women at any point of the flow diagram (Fig 2) to explore their opinion and experiences of the study procedures and intervention. Additionally, we will conduct interviews with the IPV counsellors (midwives in Denmark and psychologist and midwives in Spain) to explore their experiences with the delivery of the intervention and their opinion about a future full-randomised controlled trial. A semi-structured interview guide will be developed for the interviews using the Model for Assessment of Telemedicine Applications (MAST) as theoretical framework [38] with focus primarily on the following domains: users’ perspectives, their safety, ethical and organisational aspects; health problems and technology. All participants will give written consent prior to the interviews starting and data collection will stop once data is saturated. The interviews will be conducted in Danish/Spanish and audio recorded, and will be transcribed and analysed by use of a thematic content analysis using a combined inductive-deductive approach [39]. A coding frame will be developed, and themes will deductively be derived from MAST and supplemented with categories that inductively arise from the data. See Fig 1 for an overview of intervention and assessments.

Data will be collected by trained health personal and researchers in the STOP (Stop Intimate Partner Violence in Pregnancy, https://stop-ipv.eu) Project. On reasonable request, protocol, data collection forms and plans for statistical analysis will be available from investigators. In case of failure to provide data in the follow-up assessments, we will follow the above described STOP protocol for follow up. In Spain, the participant will be contacted by the preferred mean: phone or email. If a woman indicates she wants to be contacted by phone, the psychologist will make a maximum of three phone calls at different times and days. If the contact is made by email or phone message, the counsellor will send a maximum of two attempts leaving between both at least three days. In Denmark, women in the project will indicate if they prefer to be contacted by phone or email at the inclusion. If an included woman is unreachable, a project midwife will try to establish contact at 3 different occasions within 6 weeks. Rate of failure to obtain data will be one of the outcome measures.

Relevant concomitant care and interventions that are permitted during the trial: Women in both the intervention and control groups would be able to benefit from the standard care available for women exposed to IPV thorough the usual provision made by social and health services at any time during the study, if necessary. Indeed, one of the video-counselling sessions will be dedicated to inform women about the available resources in their community. IPV counsellors will specify if women in the intervention and the control group are in need of these resources during the time of the pilot as a valuable information for the future full-scale trial.

To accomplish the objectives, we will collect the following information:

Primary outcome:

Number of IPV positive women, who consented to receive e-health package and consented to randomization in the control group computed as a rate.

Secondary outcomes:

Number of women who consented to receive e-health package computed as a rate.Number of women in the intervention group where complete outcome data were obtained computed as a rate.Number of women in the control group where complete outcome data were obtained computed as a rate.Number of women where there was a study protocol violation computed as a rate.Recruitment duration (in days) to get the pilot sample (5 women for the intervention group and 5 women for the control group, in each country).Benefit of the intervention perceived by women through the information obtained in qualitative interviews.Perception about the duration of delay (the duration in the future full-scale trial will be determine according to the observations derived of the pilot study and the information provided in the qualitative interviews).Reasons for acceptability, non-adherence, and obstacles to recruitment, randomisation, consent and follow-up (through qualitative interviews).

Participant timeline

The participant timeline is illustrated in Fig 1.

